### **Sampling and Sample Size Calculations**

Sample size calculation:

- Participants will be recruited via convenience sampling and the size estimation was calculated using the population proportion formulae.
- the percentage of cardiorespiratory physiotherapists =  $113/19,135 \times 100\% = 0.6\%$
- the sample size formula for a single proportion is:

Where:  $z = 1.96$  p

= 0.006 or 0.6%

delta = 0.02 (within 1% of the true value)

So,  $N = 57$

Addition of 30% non-response rate, the total sample will be  $N = 74$  physiotherapists.

$$n = \left( \frac{z}{\Delta} \right)^2 p (1 - p)$$

$n$  = number of samples

$z$  = 1.96 (for  $\alpha$  error 0.05, two tailed or 95% CI)

2.58 (for  $\alpha$  error 0.01, two tailed or 99% CI)

$p$  = proportion of disease or factor under study

$\Delta$  = width of the confidence interval

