### **Methods**

A two-phase research design will be executed: (i) the first phase is a cross-sectional web survey will be conducted to explore the current practice amongst physiotherapists treating patients following major abdominal surgery in Malaysia hospitals and eventually develop a protocol for prehabilitation program; and (ii) the second phase will be a prospective, double-blinded randomized controlled trial (RCT) which aims to determine the potential effect of HIIT on multi-domain recovery. For the web survey, 74 Malaysian physiotherapists will be recruited to complete this survey. For the RCT, a total of 70 participants will be recruited from the surgery and anaesthetic clinic at the Hospital Canselor Tunku Muhriz. Participants will be randomly allocated to either receive HIIT or MICT (control group) with 35 participants in each group. Both groups will receive body conditioning and respiratory muscle strength exercises. For the intervention group, participants will receive HIIT and the control group MICT. This will be one-hour therapist-supervised intervention sessions for at least 4 weeks of exercise duration with 2 sessions per week before the surgery. The patient will be assessed at baseline, before the operation, before discharge and 4 weeks postoperatively and 3 months postoperatively. The outcomes will be assessed using multi-domain recovery measures that include physical measures (6MWT), Short Physical Performance Battery and 1 minute Sit to Stand), upper limb strength (Hand Grip Test), fatigue (Fatigue Severity Scale), psychological recovery (the Hospital Anxiety Depression Scale (HADS) and health-related quality of life (EuroQoL). Data will be analysed using intention-to-

treat analysis. The changes from all timelines in the secondary outcomes will be analysed using the Mixed Model ANOVA test.

**Result:** The findings of this research will inform guidelines of prehabilitation in determining the optimal dosage of exercise prescriptions/intensity for patients undergoing major abdominal surgery.

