## Data collection

A questionnaire was borrowed from Patman et al (2017), and Aldhuhoori et al (2021) a previous study with similar objectives completed in Australia and United Emirate Arabs. The questionnaire will be modified slightly based on current evidence with the consent of the origin to produce the final version. The questionnaire had 51 questions cutting across 7 sections that investigated the assessment tools and interventions and explored current practice amongst physiotherapists treating patients following abdominal surgery in Malaysia hospitals. The questionnaire will be divided into seven sections, including: i. participants' information, ii. patient demographics, iii. patient-physiotherapy factors for commencing treatment, iv prescription and v. dosage of interventions, vi. mobility prescription following abdominal surgery (frequency, intensity, and duration of mobility prescription), and vii. discharge planning.

The questionnaire will be validated to identify any problems with the English version web survey among a group of volunteers of 10% of physiotherapist from HTCM who has not treated other than cardiorespiratory patient. Following validation of the questionnaire, 74 participants will be invited and directed to questions in each section based on their preceding answers. Most of the questionnaire will be close-ended, incorporating a ranking system and matrix scale, with some open-ended questions to allow respondents to elaborate as appropriate. A link of the web survey will be distributed to potential participants and informed consent will be obtained upon their response. After two weeks, a reminder email will be resent again. Figure I the research flow chart for study 1.

Figure I

[figure not shown]

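### The Phase 1 survey size is derived from the 0.6% share of physiotherapists who are cardiorespiratory, which the survey cannot estimate, and its delta is defined as a full width but used as a half-width

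*Protocol*

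**What the plan says.** The Phase 1 section Sampling and Sample Size Calculations uses n = (z/Δ)² p(1 − p), with z = 1.96 ("error 0.05, two tailed or 95% CI"). The key to the formula defines p as the "proportion of disease or factor under study" and Δ as the "width of the confidence interval".

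The value entered for p is "the percentage of cardiorespiratory physiotherapists", 113/19,135 = 0.6%. Delta is given as "delta = 0.02 (within 1% of the true value"). The result is N = 57. The size is then raised: "Addition of 30% non-response rate, the total sample will be" 74. Recruitment is by convenience sampling.

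The neighbouring sections bear on this as follows:
- **Phase 1, Exclusion Criteria** removes physiotherapists who treat patients other than cardiorespiratory ones.
- **Phase 1, Statistical Analysis** plans descriptive statistics on the questionnaire answers, mainly percentages and means.
- **Abstract, Methods** states that "74 Malaysian physiotherapists will be recruited to complete this survey".
- **Phase 1, Data collection** states that "74 participants will be invited and directed to questions in each section based on their preceding answers".

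**The concern.** A precision-based sample size should rest on a quantity that the study will estimate. Here the input describes how large one specialty is within the profession. Because the survey admits only that specialty, its respondents carry no information on the 0.6%. What the survey will report is the proportion of respondents who follow a given practice, and the protocol gives neither an expected value nor a precision for any such proportion.

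The statement of precision is also inconsistent with the formula. A full interval width of 0.02 does mean within 1 point either side, so the label and the definition of Δ agree with each other. The formula, however, treats Δ as the distance from the estimate to one limit.

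At stake is how the survey percentages are read. The sections on Phase 1 and on the link between the phases present the survey as the benchmark of Malaysian practice for the control arm. A reader who meets the 1% statement could credit those percentages with a precision that the sample size was never designed to give.

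**Working it through.** **Inputs from the protocol:** z = 1.96; p = 0.006 (unrounded 113/19,135 = 0.005905); Δ = 0.02; non-response 30%; 74 invited (Data collection) or 74 completing (Abstract).

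**Assumptions not in the protocol:** an answer proportion of 50%, with 10% to show the range; and, for one variant only, an eligible population of 113.

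**1. Reproducing the plan's figures**
- (1.96/0.02)² × 0.006 × 0.994 = 9,604 × 0.005964 = 57.3, stated as 57. The unrounded p gives 56.4, which rounds up to 57.
- 57 × 1.3 = 74.1, stated as 74.

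Both figures follow from the stated inputs.

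**2. What Δ = 0.02 delivers**
- In this formula Δ is the half-width, so 57 responses give ±2 points at p = 0.006.
- The interval runs from 0.6 − 2 = −1.4% to 0.6 + 2 = 2.6%, so its lower limit is below zero.
- The expected count among 57 is 57 × 0.006 = 0.34, too small for the normal approximation behind the formula.
- For ±1 point (a full width of 0.02): (1.96/0.01)² × 0.005964 = 38,416 × 0.005964 = 229.1, so 230.

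**3. Nominal precision for a practice answer**

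Half-width = 1.96 × √(p(1 − p)/n). With the finite-population variant it is multiplied by √((113 − n)/112).

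| Responses | p = 50% | p = 10% | p = 50%, if only 113 are eligible |
|---|---|---|---|
| 52 | ±13.6 | ±8.2 | ±10.0 |
| 57 | ±13.0 | ±7.8 | ±9.2 |
| 74 | ±11.4 | ±6.8 | ±6.7 |

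All entries are percentage points.

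**4. Non-response**
- If 74 are invited and 30% do not answer: 74 × 0.7 = 51.8, about 52 responses, below the 57 calculated.
- To keep 57: 57/0.7 = 81.4, so 82 invitations.
- If 74 is the number who complete the survey, as the Abstract has it, there is no shortfall.

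**The case against.** The strongest case for leaving the section alone is that Phase 1 is a descriptive convenience survey. It has no hypothesis test or decision threshold, and 74 is a workable size for it. The arithmetic is right, and the protocol nowhere claims a precision of 1 or 2 points for a practice answer. The comparator programme is already set out in the Phase 2 section on standard care, so little hangs on the survey's precision. All of this stands. It limits the consequence but does not make the 0.6% a relevant input or reconcile the definition of Δ with the formula.

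Some stronger readings are tempting, and the protocol does not support them:
- **That 0.02 and 1% simply contradict each other.** They agree if Δ is a full width, which is how the protocol defines it. The conflict is with the formula.
- **That 113 is the population surveyed.** The protocol uses 113 only as the numerator of a percentage. The inclusion criterion admits any qualified physiotherapist who has treated patients after abdominal surgery in Malaysian hospitals, the exclusions remove those mainly in administration, and invitations may be forwarded. The size of the eligible group is not given.
- **That the true margin is always at least five times the calculated one.** Against ±2 points, 74 responses at 50% give 11.4/2 = 5.7 times, but 6.8/2 = 3.4 times at 10%, and 6.7/2 = 3.4 times at 50% if only 113 are eligible.
- **That the survey will end with 52 responses.** The Abstract and the Data collection section differ on what 74 counts, so this is one of two possible outcomes.

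**Conclusion.** The point holds. The sizes 57 and 74 are computed correctly from an input unrelated to what the survey reports, and the stated precision is not what the formula gives: 57 corresponds to ±2 points around 0.6%, and ±1 point would need 230.

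For the answers that will be reported, the nominal 95% margin is about ±13 points with 57 responses and ±11 with 74 at an assumed 50%. At an assumed 10% it is ±7.8 and ±6.8. If 113 were the whole eligible population, the 50% figures would fall to about ±9 and ±7. With convenience sampling and forwarding, all of these are nominal, since they describe random sampling error and not self-selection.

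The consequence is confined to the justification and reading of Phase 1. The trial's sample size rests on the six-minute walk test and does not use the survey.

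**What to change.** In the Phase 1 sample size section:
- Delete the calculation with p = 0.006 and the statement about being within 1% of the true value.
- Keep 74 as the target and state the nominal 95% margin for a practice proportion: about ±11 points at 50% with 74 completed responses. Say that the 50% is an assumption and that convenience sampling makes the margin nominal.
- Make the Abstract and the Data collection section agree on whether 74 counts completed surveys or invitations. If invitations, expect about 52 responses at 30% non-response (about ±13.6 points at 50%), or plan 82 invitations to keep 57.

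The cost is one rewritten paragraph and one reconciled sentence. The ethics approval letter for JEP-2024-527 lists 74 for the web survey and requires changes to be approved, so any number above 74 should be checked against it first. The survey was scheduled for October 2024 to October 2025. If it has closed, the justification can still be corrected and the margin for the achieved number of responses reported.

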## Data collection

A questionnaire was borrowed from Patman et al (2017), and Aldhuhoori et al (2021) a previous study with similar objectives completed in Australia and United Emirate Arabs. The questionnaire will be modified slightly based on current evidence with the consent of the origin to produce the final version. The questionnaire had 51 questions cutting across 7 sections that investigated the assessment tools and interventions and explored current practice amongst physiotherapists treating patients following abdominal surgery in Malaysia hospitals. The questionnaire will be divided into seven sections, including: i. participants' information, ii. patient demographics, iii. patient-physiotherapy factors for commencing treatment, iv prescription and v. dosage of interventions, vi. mobility prescription following abdominal surgery (frequency, intensity, and duration of mobility prescription), and vii. discharge planning.

The questionnaire will be validated to identify any problems with the English version web survey among a group of volunteers of 10% of physiotherapist from HTCM who has not treated other than cardiorespiratory patient. Following validation of the questionnaire, 74 participants will be invited and directed to questions in each section based on their preceding answers. Most of the questionnaire will be close-ended, incorporating a ranking system and matrix scale, with some open-ended questions to allow respondents to elaborate as appropriate. A link of the web survey will be distributed to potential participants and informed consent will be obtained upon their response. After two weeks, a reminder email will be resent again. Figure I the research flow chart for study 1.

Figure I

[figure not shown]

## Study Method

- Prior to use, 7 (10%) independent individuals will be identified to validate the survey questionnaire for readability and face validity
- The participants will be from physiotherapists with a particular interest and knowledge regarding major abdominal surgery and health professional in a different field of work.
- The main objective to identify any unanticipated problems and ambiguity within the instructions and questions and recognize time commitments required to complete the survey, allowing modification prior to dissemination.

A questionnaire was borrowed from Patman (2017) and Aldhuhoori (2021) a previous study with almost similar objectives completed in Australia and United Arab Emirates(UAE). The questionnaire was modified slightly with the consent of the origin to produce the final version. The questionnaire had 151 questions cutting across 7 sections that investigated the assessment tools and interventions and explored current practice amongst physiotherapists treating prehabilitation patients following abdominal surgery in Malaysia hospitals. The questionnaire collected participants' information, patient demographics, patient-physiotherapy factors for commencing treatment, prescription and dosage of interventions, mobility prescription following abdominal surgery (frequency, intensity, and duration of mobility prescription), and discharge planning. The questionnaire is generally close ended, incorporating a ranking system and matrix scale.

## Statistical Analysis

- Data collected from the web survey were analysed with descriptive statistics, using version 29.0 of Statistical Package for the Social Sciences (SPSS) (IBM Corporation, New York, United States of America).
- Categorical data will be analysed descriptively in terms of count, frequency and proportions, primarily reporting percentages and means, specifically clarifying the total responses (n).

- Means will be used to decipher the matrix styled questions. a 5-point likert scale will be used, aligning with “never” to “always”.
- For ranking styled questions, respondents will limit to three responses, allowing greater control of bias.

## **Phase 2 (Randomized Control Trial Study)**

The recruitment of all 70 participants is expected to be completed by July 2026, with data collection concluding by October 2026. The study results are anticipated in November 2026, and manuscript preparation is projected for completion by December 2026.

### **Study Location**

The study will be conducted in Hospital Canselor Tuanku Muhriz, Universiti Kebangsaan Malaysia in Cheras, Kuala Lumpur.

### **Study population**

#### **Inclusion criteria**

- Adults aged 18 and above.
- Scheduled for major abdominal surgery.
- Able to perform the Six-Minute Walk Test (6MWT).
- Provide written informed consent.

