The current literature highlights the significant impact of prehabilitation on improving patient outcomes in the context of major abdominal surgery. Prehabilitation programs incorporating aerobic, resistance, and breathing exercises, alongside education and lifestyle counselling, have been shown to enhance cardiorespiratory fitness, reduce postoperative complications, and expedite recovery. While moderate-intensity continuous training (MICT) is

commonly used in such programs, high-intensity interval training (HIIT) has emerged as a time-efficient and potentially superior alternative, particularly in improving VO2 max and preserving muscle mass.

Despite these findings, there is a lack of standardized exercise protocols tailored to the prehabilitation phase for patients undergoing major abdominal surgery. Additionally, limited data exist on the health status and functional outcomes of these patients throughout the surgical timeline. This gap warrants further investigation into the comparative effectiveness of HIIT and MICT, particularly in terms of their impact on multidomain recovery. By addressing these research gaps, this study protocol aims to provide valuable insights into optimizing prehabilitation strategies, ultimately improving the quality of care and recovery outcomes for patient

s undergoing major abdominal surgery.

Therefore, this study intended to evaluate the effectiveness of HIIT over MICT prehabilitation training on cardiorespiratory fitness and maximum inspiratory pressure among patients undergoing major abdominal surgery. This study also aims to investigate the effectiveness of HIIT versus MICT prehabilitation training on physical performances, upper limb strength, body composition, fatigue, psychological and health-related quality of life. We hypothesize that a 4-week HIIT program during prehabilitation is non-inferior to MICT in improving the targeted outcomes following major abdominal surgery, meaning the difference between the two interventions does not exceed the pre-specified non-inferiority margin ( $\Delta$ ).

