## **Blinding and allocation**

Patients and outcome assessors, will remain blinded to treatment allocation. However, the treating physiotherapists cannot be blinded due to the nature of the intervention. To maintain blinding, details of the intervention will not be recorded in the medical records. Outcome assessments will be conducted by a blinded assessor based off-site from the outpatient department, ensuring impartiality in both inpatient and outpatient settings. Intervention sessions will occur on different days from those scheduled for outcome assessments to further reduce the risk of unblinding. If a participant from the intervention group discloses details of their intervention to the assessor, this will be documented and reported, with the rationale recorded. All analyses will be performed on an intention-to-treat basis once randomization is unblinded.

Following recruitment and baseline assessments, participants will be randomly assigned to one of two groups which will be control group (MICT) or the intervention group (HIIT) using a computer-generated random number sequence. Allocation will be conducted by an independent individual utilizing a block randomization method (5 blocks of 14). An administrative assistant, independent of the trial, will prepare 70 sequentially numbered opaque envelopes, each containing a group allocation. A physiotherapist, trained in the study protocol, will deliver the intervention. Participants in the control group will receive moderate-intensity continuous training (MICT), while those in the intervention group will engage in high-intensity interval training (HIIT) preoperatively. Both groups will commence and conclude sessions with a warm-up and cool down to mitigate the risk of adverse events.

This study is will be conducted at a teaching hospital of the Hospital Canselor Tuanku Muhriz, Malaysia. Prospective consecutive patients will be invited to participate in the study prior to elective major abdominal surgery from February 2025 to July 2026. Fig 2 summarises the design of the trial, and each of the trial's aspect is described in detail below.

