## **Study Method**

### **Intervention care group (HIIT)**

Participants in the intervention group will receive the same care as the standard care group. Additionally, for aerobic exercise this will be a moderate intensity which is 55-75% of maximum heart rate (MHR) in week one, with graduation to high intensity in week two on > 80% of MHR [24]. Aerobic exercise training (eg: Treadmill, Cycle ergometer, body weight exercises) 1-3 times per week (30 minutes) for an overall duration typically 2-4 weeks prior to the date of surgery. Patients' Maximum Heart rate ( $210 - \text{age}$ ) and Karvonen Formula will be used for the targeted heart rate. Patients' heart rate will be monitored along the aerobic training using a smartwatch. However, those patients who are on beta-blockers or with underlying cardiac conditions, training intensity will be guided by the Rating of Perceived Exertion (RPE) between 16-18 RPE score, with appropriate adjustments made to ensure safety. The interval training will be 30-60 seconds of high-intensity training with 1- 2 minutes of active recovery (light activity or complete rest) between intervals to facilitate recovery. This will be repeated for a total of 5-10 cycles [32].

In addition to aerobic training, participants will receive the same progressive resistance exercise and inspiratory muscle training, with intensity matched to that of the standard care of

MICT group. Aim for a total session duration of about 20-30 minutes, including warm-up and cool-down. This includes 10-15 minutes of HIIT, depending on the patient's tolerance. Sessions will be done 1-3 times per week, with rest days in between to allow for recovery. Participants will also receive an illustrated handout to guide continued training support by caregivers, including recommendations on maintaining a standard amount of aerobic and strength exercise per week. A detailed session attendance checklist and vital signs will be recorded at each session to monitor adherence.

All other aspects of patient care such as preoperative management, general anaesthesia, intraoperative ventilation settings, fluid administration, prophylactic antibiotic use, pain management, management of lines and drains, general nursing care, and discharge planning will be administered at the discretion of nurses and physicians in accordance with routine clinical practices at hospital for both groups.

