## 2. Patient Eligibility Screening

Step 1: Check if the patient is awaiting major abdominal surgery.

Yes: Proceed to the next step.

No: Exclude from study.

Step 2: Check if patients Medically unstable or severe comorbidities that contraindicate exercise (e.g., unstable cardiovascular disease), Impaired cognition or confusion and impaired vision, cognition or physical impairment (UL and LL) in functional task components

Step 3: Conduct additional baseline assessments (e.g., medical history, strength, flexibility, respiratory function) for patients included in the study.

Step 4: Obtain informed consent from eligible patients.

Step 5: Randomize patients into the HIIT or MICT intervention groups.

End -Complete the screening and recruitment process.

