## Data collection

Demographic data and preoperative, intraoperative, and postoperative variables will be collected from participants and their medical records. Baseline assessments will be conducted 4 ( $\pm 1$ ) weeks in outpatient setting following referral for exercise based prehabilitation prior to date of surgery. Follow up assessment will continue to 2 days ( $\pm 1$ ) before operation in the inpatient setting, prior to discharge, 4 -weeks, and 12-week post operatively. These follow-ups will take place in the research room within the physiotherapy unit.

All measurements will be conducted by an independent, trained assessor located off-site, who will remain blinded to group allocation. Face-to-face administration of follow-up tests and questionnaires will be performed by outcome assessors at four time points: preoperatively, prior to discharge, 4 weeks, and 3 months postoperatively, to maintain consistency across participants.

Post-hospital discharge follow-ups will be contacted via phone. Participants who cannot be reached by phone for 14 consecutive days from the scheduled assessment date will be considered lost to follow-up for post-discharge outcomes.

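### The 3-to-5-week baseline window cannot hold the 4-week programme named in the hypothesis over much of its range, although it does fit the 2-4 weeks in the delivery sections

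*Protocol*

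**What the plan says.** **Entry.** The RCT inclusion criteria require that the patient is "Scheduled for major abdominal surgery". The exclusion criteria give no waiting time. The flowchart asks "Step 1: Check if the patient is awaiting major abdominal surgery" and takes yes or no for an answer.

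**Visits.** Under Data collection (Phase 2), "Baseline assessments will be conducted 4 ( $\pm 1$ ) weeks in outpatient setting" before surgery; Fig. 1 gives the same window as 3-5 weeks. The pre-operative assessment is 2 (±1) days before the operation. Randomisation follows baseline (Blinding and allocation), so supervised training cannot start earlier. The same section states: "Intervention sessions will occur on different days from those scheduled for outcome assessments".

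**Programme length, version A.** The Abstract describes supervised sessions "for at least 4 weeks of exercise duration with 2 sessions per week before the surgery". The Introduction states: "We hypothesize that a 4-week HIIT program during prehabilitation is non-inferior to MICT". Statistical analysis dates the post-prehabilitation visit at 4 weeks.

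**Programme length, version B.** The HIIT and MICT sections give a typical duration of 2-4 weeks at 1-3 sessions per week. Fig. 1 also shows an intervention period of 2-4 weeks.

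**Intensity.** HIIT begins at moderate intensity, "with graduation to high intensity in week two". MICT begins at low intensity and then moves to moderate.

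**The concern.** The visit windows fix how much calendar time a participant can have between baseline and the pre-operative assessment. If that time is shorter than the programme in the hypothesis, a participant who meets every entry and visit rule still cannot complete that programme.

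Two things are at stake. The first is the label on the result: an estimate from participants with, say, 18 to 20 days available is not an estimate for a 4-week programme. The second is the contrast between arms. High intensity is reached only from week two, so in the HIIT arm a shorter wait removes target-intensity time while the lead-in week stays. If this narrows the difference between arms, it matters more in a trial whose stated hypothesis is non-inferiority and whose analysis is by intention to treat, because similar arms support the claim.

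**Working it through.** **Inputs**
- Baseline B days before surgery: 4 ± 1 weeks = 21 to 35 days, which agrees with the 3-5 weeks in Fig. 1. That is 15 whole days.
- Pre-operative assessment P days before surgery: 2 ± 1 = 1, 2 or 3.
- Programme length: 28 days (Abstract, Introduction, Statistical analysis), or 14 to 28 days (HIIT and MICT sections, Fig. 1).

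**Time available.** Elapsed days between the two assessments = B − P.

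| Baseline | P = 1 | P = 2 | P = 3 |
|---|---|---|---|
| B = 21 | 20 | 19 | 18 |
| B = 28 (nominal) | 27 | 26 | 25 |
| B = 35 | 34 | 33 | 32 |

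**A 28-day programme.** The condition is B − P ≥ 28, so B ≥ 28 + P.
- P = 1: B ≥ 29; days 21-28 fall short, 8 of 15.
- P = 2: B ≥ 30; days 21-29 fall short, 9 of 15.
- P = 3: B ≥ 31; days 21-30 fall short, 10 of 15.

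A participant assessed at exactly four weeks falls short in all three cases. With no deduction for the pre-operative visit, days 21-27 still fall short, 7 of 15.

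**Shorter programmes.** For 14 days, B ≥ 14 + P is at most 17, so all 15 days fit. For 21 days, B ≥ 22 to 24, so 1 to 3 of 15 fall short.

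**Reading four weeks as eight sessions.** The Abstract's two sessions per week for four weeks gives eight sessions. First to last session is assumed to span 22 to 25 calendar days. Sessions may not fall on assessment days, so the usable days are B − P − 1. At P = 2:
- span 22: B − 3 ≥ 22, so B ≥ 25; days 21-24 fall short, 4 of 15.
- span 25: B − 3 ≥ 25, so B ≥ 28; days 21-27 fall short, 7 of 15.

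Letting P run from 1 to 3 widens this to 3 of 15 (span 22, P = 1: B ≥ 24) up to 8 of 15 (span 25, P = 3: B ≥ 29).

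**Sessions at the short end.** At B = 21 and P = 2 there are 21 − 3 = 18 usable days.
- At two per week: 18 × 2/7 = 5.1, so 5 or 6 sessions against eight. From week two, 11 × 2/7 = 3.1, so 3 or 4 against six (three weeks × two).
- At three per week, the top of the range in the delivery sections: sessions on days 1, 3, 5, 8, 10, 12, 15 and 17 make eight, five of them from week two.

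The loss in session count therefore depends on which frequency applies, and the protocol gives two.

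**The case against.** **The window fits the text that governs delivery.** Fig. 1 is coherent by itself: baseline at 3-5 weeks, intervention of 2-4 weeks, then the pre-operative assessment. The HIIT and MICT sections agree with it, and under that text no baseline day falls short. This stands. A reader might infer that much of the window enrols patients who cannot receive the tested intervention; that takes one of two conflicting lengths as settled, and the protocol settles neither. What remains is that the hypothesis, Abstract and analysis label do not match the window.

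**The missing entry criterion is partly covered.** Baseline must be at least three weeks before surgery and precedes randomisation, so shorter waits have no in-window baseline. This also stands: a lower limit exists, but it is not one that guarantees four weeks.

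**Stricter counts are possible.** Requiring 28 training days strictly between the assessments gives B − P − 1 ≥ 28, so 9 to 11 of 15 fall short, and 10 (67%) at the nominal visit. Nothing in the protocol says that a 4-week programme at two sessions per week needs 28 such days, so this should not be the headline. Nor is 67% a share of patients: no waiting-time distribution is given.

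**Both arms ramp up.** MICT also spends week one below its target intensity, so a short wait trims both arms. It would be tempting to say that the window biases the trial towards non-inferiority. Some narrowing is plausible, but its size is not established. Attendance is recorded in both arms, so exposure will at least be known.

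**Conclusion.** The point holds as an internal contradiction with a consequence for what can be concluded. The window cannot hold the 4-week programme stated in the Abstract, Introduction and Statistical analysis for 8 to 10 of 15 permitted baseline days if 28 elapsed days are required. The figure is about 4 to 7 of 15, at the nominal pre-operative visit, if eight sessions spanning an assumed 22 to 25 days are enough. On the first reading even the nominal baseline day falls short. The 2-4 weeks in the HIIT section, the MICT section and Fig. 1 fits throughout.

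As written, a result from this window cannot be described as the effect of a 4-week programme. The trial can still run. The counts rest on whole calendar days and assume that training starts only after baseline and ends before the pre-operative assessment.

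**What to change.** Reconcile the programme length in the Abstract, Introduction and Statistical analysis with the HIIT and MICT sections and Fig. 1, and reconcile both with the baseline window in Data collection and Fig. 1. Which length is retained is the sponsor's decision.

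- **If the 3-5 week window is kept:** restate the hypothesis, the Abstract and the 4-week label on the post-prehabilitation visit to the programme length that the window can deliver. This is a text amendment and costs no patients.
- **If 4 weeks is retained:** make the baseline window consistent with it, allowing for the pre-operative assessment, and put the matching interval to planned surgery into the inclusion criteria and Step 1 of the flowchart, checked before randomisation. This would cost recruitment. The July 2025 ethics amendment approval already records a limited number of eligible patients as the reason for dropping a walking-distance criterion, and this is a single-site trial. The cost cannot be sized without the distribution of waiting times.
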